# Technology-enhanced multi-domain at home continuum of care program with respect to usual care for people with cognitive impairment: the Ability-TelerehABILITation study protocol for a randomized controlled trial

**DOI:** 10.1186/s12888-016-1132-y

**Published:** 2016-11-25

**Keywords:** Telerehabilitation, Dementia, Mild cognitive impairment, Alzheimer’s disease, Continuum of care

## Abstract

**Background:**

According to the World Alzheimer Report (Prince, The Global Impact of Dementia: an Analysis of Prevalence, Incidence, Cost and Trends, 2015), 46.8 million people worldwide are nowadays living with dementia. And this number is estimated to approximate 131.5 million by 2050, with an increasing burden on society and families. The lack of medical treatments able to stop or slow down the course of the disease has moved the focus of interest toward the *nonpharmacological approach* and *psychosocial therapies* for people with/at risk of dementia, as in the Mild Cognitive Impairment (MCI) condition. The purpose of the present study is to test an individualized home-based multidimensional program aimed at enhancing the continuum of care for MCI and outpatients with dementia in early stage using technology.

**Methods:**

The proposed study is a single blind randomized controlled trial (RCT) involving 30 subjects with MCI and Alzheimer’s disease (AD) randomly assigned to the intervention group (Ability group), who will receive the “Ability Program”, or to the active control group (ACG), who will receive “Treatment As Usual” (TAU). The protocol provides for three steps of assessment: at the baseline (T_0), after treatment, (T_1) and at follow-up (T_2) with a multidimensional evaluation battery including cognitive functioning, behavioral, functional, and quality of life measures. The Ability Program lasts 6 weeks, comprises tablet-delivered cognitive (5 days/week) and physical activities (7 days/week) combined with a set of devices for the measurement and monitoring from remote of vital and physical health parameters. The TAU equally lasts 6 weeks and includes paper and pencil cognitive activities (5 days/week), with clinician’s prescription to perform physical exercise every day and to monitor selected vital parameters.

**Discussion:**

Results of this study will inform on the efficacy of a technology-enhanced home care service to preserve cognitive and motor levels of functioning in MCI and AD, in order to slow down their loss of autonomy in daily life. The expected outcome is to ensure the continuity of care from clinical practice to the patient’s home, enabling also cost effectiveness and the empowerment of patient and caregiver in the care process, positively impacting on their quality of life.

**Trial registration:**

ClinicalTrials.gov ID: NCT02746484 (registration date: 12/apr/2016 – retrospectively registered).

## Background

Dementia is now considered as a social emergency since it became one of the 25 main causes of disability in people worldwide over the last few decades [25]. Dementia affects multiple domains, such as cognitive functioning, behavioral aspects and functional skills. It has also a significant impact on personal autonomy in daily life and social relationships, associated to a high level of caregiver burden as indicated by data from 2015 World Alzheimer Report [28]. The most common form of dementia is Alzheimer’s disease (AD), a progressive neurodegenerative condition accounting for up to 60% of all dementia cases [38]. From the clinical and health management point of view, Mild Cognitive Impairment (MCI) and early stages of AD represent the most interesting clinical conditions. MCI is considered a condition at risk for the development of dementia, therefore early interventions can be essential to prevent or delay further decline. Currently, no pharmacological therapies are available to prevent a potential conversion from MCI to AD condition or to change the AD course. However, different types of non pharmacological interventions have been developed and an increasing body of evidence shows that cognitive stimulation programs bring benefits to cognitive function of people with mild to moderate dementia over and above any medication effects [6, 39]. Within the framework of non pharmacological interventions, the use of technology to assist the person at risk and/or with mild dementia at home and to extend rehabilitation services in the treatment of dementia has gradually gained importance. It provides a range of home services based on innovative technologies which include therapeutic interventions, remote monitoring of progress and training for caregivers of people with disability [18]. These long-distance rehabilitation services were primarily developed in order to provide equitable access to local sanitary systems for individuals who are geographically remote or with physical disabilities for whom it is difficult to reach the hospital [35]. Nowadays, as long as the potential benefits of telerehabilitation have been highlighted in the literature [2], these technologies are also being applied to cognitive rehabilitation. In fact, unlike usual face-to-face care rehabilitation protocols, these technological approaches appear to be more advantageous in terms of intensity and duration of treatment, lowest costs and support of dyad (patient and caregiver) at home [11, 20].

Nonetheless, the efficiency and efficacy of home-based technology-enhanced continuum of care programs are poorly examined and evidences are controversial. Moreover, functional skills, level of patient engagement at home and psychological well-being are under-investigated despite their being key outcomes of interest [21]. Randomized controlled trials (RCT) are strongly needed to determine the optimal design of home-based treatment protocols and identify their long-term benefits.

The main aim of the proposed trial is to test the performance of a technology-enhanced rehabilitation and telemonitoring program (The Ability Program) to ensure the continuity of care from clinical setting to patient’s home. We will investigate whether MCI and people with early AD participating in the Ability program will show improvements in cognition and quality of life (outcome evaluation; efficacy) and better adherence and engagement in the program (output evaluation; efficiency) with respect to MCI and AD subjects taking part in the TAU.

## Methods

### Study design

The design is a single-blind, randomized, two-treatment arms (Ability Program, over 6 weeks vs. TAU, over 6 weeks) controlled clinical trial. After enrollment and baseline assessment, MCI and AD subjects will be randomized (with an allocation ratio of 1:1) into either the Ability group (30 motor-cognitive rehabilitation sessions combined with the measurement and monitoring from remote of vital parameters delivered at home through the Ability platform) or the active control group (ACG) (30 motor-cognitive rehabilitation sessions combined with the measurement of vital parameters to be performed at home through the usual care treatment procedure). Primary and secondary outcome measures will be obtained at baseline (T_0) before starting either program, post-intervention at 8 weeks after baseline (T_1) and at follow up 12 months after baseline (T_2). Consolidated Standards Of Reporting Trials (CONSORT) flow diagram for enrollment and randomization in the TelerehABILITation study is showed in Fig. 1.

**Fig. 1 Fig1:**
[figure not shown]
CONSORT flow diagram. Consolidated Standards Of Reporting Trials (CONSORT) flow diagram for enrollment and randomization in the TelerehABILITation study

### Sample size

According to previous multicenter controlled studies [3, 14], sample size calculation was performed considering that under the assumption of normal distribution of the scores (primary outcomes differences between groups) and considering α level of .05, a sample size of 30 subjects resulted in a power greater than 70% and was therefore considered as adequate for this trial. To avoid loss to follow-up and maximize the follow-up sample, standard procedures (regular phone contacts with participants) will be applied.

### Participants

Thirty participants will be consecutively recruited from the Memory Clinic of IRCCS Don Carlo Gnocchi Foundation.

Outpatients inclusion criteria will be the following: a) diagnosis of mild AD or MCI due to AD, according to DSM- 5 diagnostic criteria and AD/MCI diagnostic criteria [23, 1]; b) MMSE score >18 (Mini Mental State Examination, [15, 22]); c) aged over 65 years and d) with school attendance ≥3 years.

Exclusion criteria will be a) severe auditory and/or visual loss; b) overt severe behavioral disturbances. and c) recent (1 month or less before starting the program) introduction or dose modification of the following pharmacological treatments: cholinesterase inhibitor, memantine, antidepressant, or antipsychotic drugs. Low-dose benzodiazepines for insomnia will be allowed during the study.

### Randomization and masking

Randomization will occur after screening and baseline assessments. Subjects will be randomly assigned to the Ability group or to the ACG with a 1:1 allocation ratio. Randomization will be conducted by an independent operator neither ot involved in the assessment and/or treatment using a computer algorithm (http://www.graphpad.com/quickcalcs/randMenu/). Since participants cannot be blinded to their treatment allocation, they will be instructed not to discuss the nature of their intervention with the researchers in charge of the assessments. Outcome measures will be collected by researchers blinded to group allocation.

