### Statistical analyses

Statistical analyses on outcome measures will be conducted using SPSS. We will look at statistically significant changes in primary and secondary outcome measures from T_0 (start of treatment) to T_1 (end of treatment), i.e. a training effect. Moreover, we will look for a treatment (Ability vs. TAU) effect and at training x treatment interactions. This will be done through a 2-way ANOVA. Post hoc analysis will be applied to compare Ability with TAU. An alpha ≤ 0.05 will be considered significant. Moreover, score modification at T_2 (after 12 months) in both groups will be evaluated by means of regression analyses over time considering previous values at baseline and T_1. Contributing factors that may predict changing in outcomes will be also examined in a multivariate interval regression analysis. Moreover, each outcome will be categorized in three intervals according to the criterion of a clinical improvement/stability/impairment which was set by expert physicians. Given the exploratory nature of the study, a stepwise forward model will be set with an entrance alpha level of 0.10. Model assumptions and goodness of fit were evaluated by means of the proportionality of odds across response categories test and the association between predicted and observed values (Spearman rho). When the proportionality of odds assumption is violated, a generalized logistic regression model will be computed. For each significant model, several representative profiles and their associated probability of a successful treatment will be computed.

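### With mild AD and MCI pooled in 30 participants, the T0–T1 treatment comparison should adjust for diagnosis and baseline score

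*Protocol article*

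**What the plan says.** All references are to the Protocol article.

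- **Participants.** Eligibility requires a "diagnosis of mild AD or MCI due to AD" and an MMSE score above 18. "Thirty participants will be consecutively recruited from the Memory Clinic". No target or cap is set for the split between the two diagnoses.
- **Randomization and masking.** Allocation follows the baseline assessment, so diagnosis is known by then. "Subjects will be randomly assigned to the Ability group or to the ACG with a 1:1 allocation ratio", by an independent operator "using a computer algorithm (http://www.graphpad.com/quickcalcs/randMenu". The section names no stratification factor and does not exclude one.
- **Statistical analyses.** Change from T0 to T1 (training), treatment, and their interaction are tested by a 2-way ANOVA, followed by post hoc comparison of the arms. Diagnosis is not one of the two factors. "An alpha ≤ 0.05 will be considered significant". T2 scores go into a regression that takes the T0 and T1 values into account. Separately, "Contributing factors that may predict changing in outcomes will be also examined" by forward stepwise selection with entry at 0.10. Those factors are not named, and that model does not adjust the ANOVA.
- **Assessment design and outcomes measures.** Participant quality of life is primary. Conversion to dementia is among the secondary outcomes.

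**The concern.** The sample mixes two diagnoses that the Background describes differently: MCI as a state of risk for dementia, AD as a progressive disease. In arms of about 15, chance can easily leave one arm with noticeably more AD participants. If the diagnoses differ in score level or in course, part of the observed arm difference is then case mix. An analysis with only time and treatment cannot separate the two, although diagnosis and baseline score are both recorded before allocation. The stepwise model may or may not select diagnosis, and it is not the efficacy test.

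**Working it through.** **1. The plan's own figure.** The Sample size section says "a sample size of 30 subjects resulted in a power greater than 70" per cent, "under the assumption of normal distribution of the scores (primary outcomes differences between groups"), at α = 0.05. It gives no effect size or SD, so the figure can be neither reproduced nor refuted. Solving backwards with 15 per arm, two-sided, normal approximation:

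d = (1.960 + 0.524) / √(15/2) = 2.484 / 2.739 = 0.91 SD (0.94 with the t distribution; 0.79 and 0.81 one-sided).

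Two-sided power is 59% at d = 0.8 and 28% at d = 0.5. The value d = 0.94 is used in step 4.

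**2. Probability of imbalance.** The AD/MCI split is not given. Assume 15 of 30 are MCI and the arms are exactly 15 and 15. The number x of MCI participants in one arm is hypergeometric:

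P(x) = C(15,x)² / C(30,15), with C(30,15) = 155,117,520.

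- 8:7 either way: 2 × 6,435² / 155,117,520 = 53.4%. So 9:6 or worse is 46.6%.
- 9:6 either way: 2 × 5,005² / 155,117,520 = 32.3%. So 10:5 or worse is 46.6 − 32.3 = 14.3%.
- If 10 or 20 of 30 are MCI, the arm counts differ by 4 or more with probability 24.5%, and by 6 or more with probability 5.0%.
- With coin-flip allocation, and 10 or 15 of 30 with AD, the arms differ by 20 percentage points or more in AD share with probability 26% to 36%, and by 33 points or more with probability 6% to 10%.

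**3. Where imbalance enters.** Let p be the between-arm difference in AD share, L the AD–MCI gap in T0 level, and G the gap in T0–T1 change. The expected shift in each planned contrast is:

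- training × treatment interaction: p·G (L cancels);
- treatment main effect, averaged over T0 and T1: p·(L + G/2);
- post hoc comparison of T1 scores: p·(L + G).

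For a 10:5 split p = 5/15 = 0.33; for 9:6 p = 3/15 = 0.20.

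**4. Effect on the interaction test.** There were 20,000 simulated trials per setting, with 15 AD and 15 MCI, 15 per arm, one change score per participant, and within-diagnosis SD of change 1. G is assumed, since the article gives no value. The power columns use a true effect of 0.94 SD.

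| G (SD) | Shift at 10:5 (SD) | Type I error, all allocations, no term | Type I error at 10:5 or worse, no term | Same, with diagnosis term | Power, no term | Power, term only | Power, strata + term |
|---|---|---|---|---|---|---|---|
| 0 | 0 | 5.0% | 4.7% | 5.3% | 69.5% | 67.7% | 70.3% |
| 0.3 | 0.10 | 5.1% | 6.0% | 5.3% | 68.4% | 67.7% | 70.3% |
| 0.5 | 0.17 | 5.1% | 7.4% | 5.3% | 66.7% | 67.7% | 70.3% |
| 0.8 | 0.27 | 5.1% | 10.3% | 5.3% | 62.6% | 67.7% | 70.3% |
| 1.0 | 0.33 | 5.0% | 11.7% | 5.3% | 59.4% | 67.7% | 70.3% |

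The term alone changes power by 67.7 − 69.5 = −1.8 points at G = 0, −0.7 at 0.3, +1.0 at 0.5, +5.1 at 0.8 and +8.3 at 1.0. Strata plus the term gain 70.3 − 68.4 = 1.9 points at 0.3, 3.6 at 0.5, 7.7 at 0.8 and 10.9 at 1.0. Baseline score was not in these simulations.

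**5. Conversion to dementia.** A participant who already has AD dementia cannot convert. If a fraction r of MCI participants convert in both arms, a rate over all participants is r × MCI share. At a 10:5 split that is r·10/15 against r·5/15, a twofold ratio with no treatment effect. This needs no assumed gap.

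**The case against.** Much of the opposing case stands.

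- **Stratification.** A reader might infer that allocation was unstratified. The article says only 1:1 and a web tool. It is a condensed account, and strata or blocks may be in the full protocol. Silence does not establish their absence, so the point rests on the analysis, where the two factors are stated.
- **Bias.** A reader might infer that imbalance passes straight into the result. In the interaction, level differences cancel and only a gap in change counts, scaled by the imbalance. Randomisation keeps the comparison unbiased on average, and overall type I error stays at 5.0% to 5.1%.
- **T2.** The 12-month analysis is not unadjusted: it already uses T0 and T1 values, which may carry part of any severity difference.
- **Prognostic strength.** Nothing in the article shows that diagnosis is the strongest predictor, or gives a gap in quality-of-life change. Entry is limited to mild AD, which narrows the contrast.
- **Size.** The likely event is the small one: 9:6 or worse has probability 47%, but a 9:6 split shifts the interaction by only 0.10 to 0.20 SD at gaps of 0.5 to 1.0. The 0.17 to 0.33 SD shift belongs to 10:5, and 10:5 or worse has probability 14%. The standard error of the arm difference is √(2/15) = 0.37 SD, so each of these shifts is below one standard error.
- **Benefit.** The diagnosis term alone loses a little power when the gap in change is small.

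What remains is that level differences do reach the treatment main effect and any post hoc T1 comparison, both of which fall within the stated plan. An imbalanced trial also has a conditional error rate that an entry variable already on file would correct.

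**Conclusion.** The concern holds as a matter of precision and conditional error, not of bias. In 30 pooled participants, a diagnostic imbalance of 9:6 or worse is close to an even chance (47%, assuming 15 MCI and equal arms). The stated T0–T1 comparison has no means of adjusting for it. A 10:5 split shifts the interaction by one third of the gap in change. Type I error in trials split 10:5 or worse is then 7.4% at an assumed gap of 0.5 SD and 11.7% at 1.0 SD, against 5.3% with a diagnosis term. Average power falls from 69.5% with no gap to 66.7% and 59.4% at those gaps. If the diagnoses do not differ in change, the interaction is unaffected. Conversion to dementia is the outcome most directly exposed if its denominator includes participants with AD.

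**What to change.** 1. Make the primary between-arm comparison at T1 an ANCOVA of the T1 score on treatment, baseline score and diagnosis (MCI v AD). Baseline score deals with level differences in a single T1 contrast, and diagnosis deals with differences in course.
2. Add diagnosis to the T2 regression, which already considers T0 and T1 values.
3. Report conversion to dementia among MCI participants only, by arm.
4. If allocation does not already use strata, have the independent operator use separate lists for MCI and AD for participants not yet randomised. The article describes the trial as ongoing, so this may help only some of them; items 1 to 3 do not depend on it.

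The cost is one or two degrees of freedom in the T1 model, one more list for the operator, and about 2 points of power from the diagnosis term under unstratified allocation if the diagnoses do not differ in change. Both covariates are recorded before randomisation, so no new data are needed. The model should be fixed before outcome data are examined by arm.

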### Intervention

The study protocol predicts the random assignment of all participants to the Ability Program or to the TAU according to a single-blind parallel-group study approach.

Both programs last six consecutive weeks and combine cognitive and motor activities with the measurement of vital parameters, all to be performed at home. According to the Individual Rehabilitation Plan (IRP), the rehabilitation protocol in both programs comprises the performing of cognitive exercises for 5 days a week and light motor activities for 7 days a week. The selection of vital parameters and frequency of their measurement is set by the clinician, according to individual diagnosis.

#### The Ability program

The Ability program is a technology-enhanced version of the home-based usual care program (TAU), with the same duration, type of rehabilitation domains (motor and cognitive), dose of respective rehabilitation sessions, prescription for the monitoring of vital parameters, with the addition of a tracking device for physical activity and sleep, and monitoring from remote of all the activities performed by the participant.

Subjects assigned to this group are provided with the Ability kit, a set of technological devices including: a tablet for the delivery of the IRP; a sphygmomanometer for the detection of blood pressure; a pulse oximeter for the measurement of oxygen blood level and heart rate; a scale for the detection of body weight, and a FitBit Charge to track physical and sleep activity.

For all the 6-week intervention, the IRP is delivered through the tablet that, every day, after opening its user-friendly dashboard, shows the activities planned by the clinician for that day. Cognitive exercises are delivered for 5 days a week, adapted motor activity is proposed for 3 days a week, while light aerobic motor activity is suggested for the remaining 4 days. At least once a week a message on the dashboard recalls subjects to measure the vital parameters critical for their clinical condition, according to medical prescription. As regards the FitBit tracker, no tablet-based recalls are predicted since participants are asked to wear it continuously (24 h) for all the 6 weeks, except for very short interruptions to recharge it (about 2 hours once a week).

#### Tablet-based cognitive and motor activities in the Ability program

Tablet-based cognitive activities aim to reinforce multiple cognitive domains: attention, reasoning, procedural, semantic and autobiographic memory, executive functions, and visual-spatial skills (see Table 1). Activities within each cognitive daily session are sequentially framed in a way that they typically begin with a learning phase in which several stimuli are proposed. Then, they typically continue with activities that stimulate attention and other cognitive functions. Finally, a recall task is proposed. Each activity is structured into five levels of difficulty that adaptively increase on the basis of subject’s performance. The total time predicted for each daily cognitive session is about 20 min.

**Table 1 Tab1:** Tablet-based cognitive activities

Main domain	Activities: examples of contents
Language	Reading and comprehension of a piece of newspaper article
	Word production from semantic category in a specific time
	Word production based on a specific letter
	Word production based on a specific syllable
	Word production from a semantic category, based on a specific letter
Memory	Recall of popular songs, films or actor’s biographies
	Memorization of daily life notes or brief messages and recall at the end of the cognitive session
	Memorization of a list of words and recall, searching for words which were not included in the list previously stored
	Recall of information in the newspaper article previously read and answering questions about it
	Carefully looking at a painting and memorizing
	Recall of information from a painting previously observed and answering some questions
	Inclusion of correct missing words in the text of some popular poems
Executive function	Putting things in the correct sequence based on a specific criterion
	Putting actions of daily life in the correct sequence
	Mathematical calculations
	Anagrams
	Rebuses (using pictures for words)
	Labyrinths
	Placing hands in empty clocks based on the time indicated in arabic figures
Attention	Finding specific words in a grid of mixed words
	Finding a specific letter in a grid of mixed letters

Aerobic physical exercises are adapted motor activities [13] that involve the performing of simple movements, e.g., shoulder rotations, arm rotations, lower limb flexion, and neck, shoulder, or arm stretching. Exercises are reported via video clips (see Fig. 2). Each activity starts with a brief explanatory training conducted by the physiotherapist that also shows the correct execution of the exercises. Then the subject starts the movements mirroring the therapist while watching the video. Soft background music in time with the activity is played to improve the synchronized movement pattern, to capture attention and to foster engagement with the task [34]. Subjects use the support of a chair in all activities, both for home safety and since they often suffer from (sub) clinical balance disturbances. The total time envisioned for each adapted motor activity is about 15 min.

